### Supplementary routine data collection

#### Baseline data

Use of hearing and visual aids will be recorded and these made available to the patient for the PACU assessments. We plan to collect standard demographic data including American Society of Anesthesiologists (ASA) score and planned surgery. Cognitive impairment is a known risk factor for the development of postoperative delirium [20] and will be used to stratify randomisation. The MOCA will be used to quantify cognitive status pre-operatively. In addition, some items from the 3D-CAM will be assessed at baseline to determine whether later errors in the 3D-CAM in PACU reflect a change from baseline performance. Pre-operative pain and anxiety will be recorded using the relevant questions from the QOR-15 questionnaire. The National Surgical Quality Improvement Programme (NSQIP) surgical risk calculator surgical complications risk [28] will also be calculated for each patient to potentially allow for risk adjustment in statistical analyses.

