## Background and rationale

There is current interest in the use of electroencephalographic (EEG)-guided administration of anaesthesia to prevent postoperative delirium and neurocognitive decline, prompted by findings of the association between low intraoperative EEG index values or burst-suppression patterns and postoperative delirium [1–3]. The underlying rationale is that reducing total anaesthetic dose and avoiding EEG suppression might improve neurocognitive outcomes. Prospective randomised clinical trials (RCTs) comparing titration of anaesthesia to processed EEG index ranges versus clinical signs have demonstrated reductions in postoperative delirium [1, 4]. However, the merit of targeting particular EEG index values or patterns, compared to purely avoiding the suppression pattern, is not known.

In our previous observational work of EEG patterns during maintenance and emergence from general anaesthesia, we have observed a variety of patterns in the EEG prior to waking [5, 6]. Although there is not a consensus among anaesthesiologists of what it means to be awake, we have started to distinguish between emergence and recovery from general anaesthesia. When we use the term ‘emergence from anaesthesia’ we are referring to the transition from surgical anaesthesia to a state with outward signs of cortical function (typically coordinated motor responses). One example would be eye contact in response to verbal or light tactile stimulation. Anaesthesia recovery is the transition from the end of emergence to normal pre-operative neurocognitive function. Defining when the actual complete period of anaesthesia has ended, and the subject has returned to a pre-anaesthesia baseline is difficult because a patient may be safe to discharge from the recovery room before all of the sedating effects of anaesthesia have subsided. Therefore, the complete recovery trajectory may go undocumented.

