**Fig. 2 Fig2:**
[figure not shown]
SPIRIT diagram demonstrating planned data collection

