##### Further clinical outcomes

Quality of recovery (day 1 and day 30) – QOR-15Modified Brice Interview (day 1 and day 30)Hospital length of stay and discharge destinationDays alive at home 30 days after surgerySerious adverse events (falls, unplanned high-dependency or intensive care unit admission, stroke or myocardial infarct, surgical site infection, hospital readmission and death) up to 12 monthsCognitive status at 12 months (telephone Montreal Cognitive Assessment (tMOCA))

The QOR-15 is a validated score reflecting overall quality of recovery from anaesthesia and surgery [22, 23]. The Modified Brice Interview [24, 25] is used to check for awareness with recall. Days alive at home (DAAH) has been chosen as a validated patient-centred outcome measure that is readily quantifiable and reflects duration of hospitalisation, discharge destination and mortality [26]. Serious adverse events will also be recorded, from patient report and note review out to 12 months postoperatively to look at longer-term recovery and later serious complications. We will also conduct a tMOCA at 12 months as a final cognitive evaluation [27].

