PACU delirium is our clinical outcome of primary interest, as a marker of neurocognitive recovery from anaesthesia. In our previous observational study, the incidence of CAM-ICU-diagnosed PACU delirium was 16% in those over 60 years and in a subsequent departmental audit, the incidence of PACU delirium diagnosed using the NuDESC tool was around 20% in those aged 65 years and over. Given that the study inclusion criteria requires > 2 h of anaesthesia, study participants will likely in general be having more extensive surgery and longer anaesthesia than those in the previous study and audit; therefore, we conservatively estimate a 20% incidence of PACU delirium in the control groups. From our observational work, the presence of EEG alpha has an odds ratio of approximately 0.5 for PACU delirium (unpublished data). Five hundred and thirty-two patients would be required to demonstrate a decrease in PACU delirium from 20 to 10% with 90% power (two-tailed alpha 0.05, beta 0.1, *χ*^2^ test). Thus, the study is powered to demonstrate strategies which have a large impact in preventing the development of delirium.

Almost certainly this study will also be sufficiently powered for minimum clinically important effects in some of the other secondary outcomes including delirium subcomponent features, days alive and out of hospital, and quality of recovery. We plan to recruit 600 patients to allow for loss to follow-up and a lower incidence of delirium than expected.

Continuous outcomes will be assessed using *t* tests and analysis of variance (ANOVA), ordinal with rank sum, and categorical outcomes will be assessed using the *χ*^2^ test, with significance set at *p* < 0.05. Non-linear mixed-effect modelling will be incorporated where appropriate to account for propensities such as: patient maximum alpha power, within-patient fentanyl and desflurane dose-response relationships and characteristics of the anaesthetic technique. Interactions between the two interventions are possible and will be examined. We also plan to carry out multivariate logistic regression to determine the major risk factors for the development of the features of PACU delirium, and receiver operator curve analysis to determine which elements of the early delirium screening tools are most closely associated with adverse clinical outcomes. *We anticipate performing further exploratory analyses in addition to those explicitly defined pre-operatively.*

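### The article describes only the pain and anxiety questions of the QoR-15 before surgery, so its day-1 and day-30 totals have no described baseline to adjust for: a modest, cheaply avoided loss of precision

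*Protocol article*

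**What the plan says.** The protocol article uses the QoR-15 in three places.

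- **Further clinical outcomes.** The list opens with "Quality of recovery (day 1 and day 30" and names the QoR-15 as the measure. The text below the list adds: "The QOR-15 is a validated score reflecting overall quality of recovery from anaesthesia and surgery".
- **Baseline data.** Before surgery, "Pre-operative pain and anxiety will be recorded using the relevant questions from the QOR-15 questionnaire". The rest of the questionnaire is not mentioned. The same section takes a pre-operative reference for another instrument: "some items from the 3D-CAM will be assessed at baseline to determine whether later errors in the 3D-CAM in PACU reflect a change from baseline". It also collects the MOCA and the NSQIP risk, the latter with possible risk adjustment in mind.
- **Statistical analysis and power calculations.** The trial is expected to have enough power for several secondary outcomes, among them "days alive and out of hospital, and quality of recovery". No standard deviation, effect size or calculation is given for the QoR-15. The general analysis rule is: "Continuous outcomes will be assessed using *t* tests and analysis of variance (ANOVA), ordinal with rank sum".

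The schedule of assessments is Fig. 2 ("SPIRIT diagram demonstrating planned data collection"). The figure is not reproduced in the text available.

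**The concern.** The questionnaire is already in use at the pre-operative assessment, yet the text describes only part of it there. The total score is then used as an outcome twice after surgery. If the remaining questions really are left out, the total cannot be adjusted for its own starting value. Whatever variation patients have in pre-operative level stays in the error term of the day-1 and day-30 comparisons.

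A baseline total is an obvious covariate for this outcome and can only be collected before the operation. An analysis plan can choose among covariates that were recorded, but it cannot create this one afterwards. The article also expects adequate power for quality of recovery without figures to support it, so an inexpensive gain in precision is worth having.

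**Working it through.** **The plan's own figures.** None is given for the QoR-15. The two stated sample sizes reproduce, and this point affects neither.

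- Alpha power (1 dB, SD 2.1, two-sided 0.05, 95% power): n per arm = 2 × (1.960 + 1.645)² × 2.1² / 1² = 114.6, so 115 per arm and 230 in total, as stated.
- PACU delirium (20% v 10%, two-sided 0.05, 90% power, no continuity correction): 266 per arm, 532 in total, as stated.

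**Inputs for the QoR-15.**

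- From the article: 600 patients, so 300 v 300 for each factor.
- Assumed: a correlation r of 0.2 to 0.5 between the baseline and follow-up totals. The documents give no value, and r need not be the same at day 1 and day 30.

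**Without a baseline.** The detectable standardised difference at 80% power is (1.960 + 0.842) × √(2/300) = 0.229 SD.

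**With the baseline total as covariate.** Residual variance is multiplied by 1 − r² and the detectable difference by √(1 − r²). The equivalent sample size is multiplied by 1/(1 − r²).

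| Assumed r | 1 − r² | Equivalent extra patients | Detectable difference, 80% power | Power at an illustrative 0.2 SD |
|---|---|---|---|---|
| no baseline | 1.00 | – | 0.229 SD | 68.8% |
| 0.2 | 0.96 | 1/0.96 = 1.04, so 4% | 0.224 SD | 70.5% |
| 0.3 | 0.91 | 1/0.91 = 1.10, so 10% | 0.218 SD | 72.8% |
| 0.5 | 0.75 | 1/0.75 = 1.33, so 33% | 0.198 SD | 80.7% |

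**Why these are upper limits.** Two things reduce the gain.

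1. The table compares adjustment with no adjustment at all. If recorded covariates already explain a share R₀² of the variance, and adding the baseline total raises this to R₁², the gain is (1 − R₀²)/(1 − R₁²). For illustration, R₀² = 0.09 and R₁² = 0.25 give 0.91/0.75 = 1.21. That is 21% more patients, against 33%.
2. Patients already enrolled would have no baseline total. With 60 of 600 in that position, average residual variance is roughly 0.9 × (1 − r²) + 0.1. At r = 0.5 this is 0.775, and 1/0.775 = 1.29. At r = 0.2 it is 0.964, and 1/0.964 = 1.04.

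**ANCOVA rather than change scores.** A change score has relative variance 2(1 − r): 1.6 at r = 0.2, 1.4 at 0.3 and 1.0 at 0.5. Over the assumed range it would do no better than ignoring the baseline.

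**The case against.** The strongest reply is that the article contradicts nothing here. It defines no change-from-baseline or return-to-baseline QoR-15 endpoint. The planned t tests, ANOVA and rank-sum tests need no baseline. Randomisation makes the arm comparison of absolute scores unbiased. The two questions asked before surgery serve another purpose, recording pre-operative pain and anxiety. All of this stands, and it limits the point to precision.

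The omission is also inferred from silence. The Baseline data section does not say the remaining questions are left out, and Fig. 2 could not be seen. This stands as a caution. Against it, singling out the relevant questions would be odd wording if the whole form were completed. If Fig. 2 does schedule the full form, the text needs only clarifying.

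Third, other covariates are available: surgery type (a stratification factor), MOCA, NSQIP risk and the two QoR-15 items themselves. That stands and is why the gain is given as a maximum.

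Finally, power may be ample anyway. At an illustrative 0.3 SD, power with 300 v 300 is already about 96%, and r of 0.3 to 0.5 raises it only to 97–99%. That too is fair: without a minimum important difference and an SD, nothing here shows the article's power statement to be wrong.

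A reader might go further and infer that the trial cannot measure recovery at all without a starting value, pointing to "Anaesthesia recovery is the transition from the end of emergence to normal pre-operative neurocognitive function". That definition concerns neurocognitive function, not the QoR-15. The article treats the QoR-15 as a score of quality of recovery in its own right, and the difference between arms can be estimated from it directly.

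**Conclusion.** The point holds as a minor design limitation of one secondary outcome. On the text shown, no pre-operative QoR-15 total is described, so the day-1 and day-30 totals cannot be adjusted for it. For r between 0.2 and 0.5, the forgone precision is equivalent to at most about 4 to 33% more patients for this outcome. It is less once other recorded covariates are used. This rests on the assumed correlation and on Fig. 2 not scheduling the full form.

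Two other inferences should be resisted. The comparison of arms is not biased by the missing baseline. It is also not true that nothing on the form has a starting value, because pain and anxiety do; the gap concerns the total score. No analysis that the article plans is made impossible.

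**What to change.** First check Fig. 2. If it already schedules a full pre-operative QoR-15, bring the Baseline data wording into line with it.

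If it does not, change the sentence on pre-operative pain and anxiety to something like: *The full QoR-15 will be completed before surgery; its pain and anxiety items also serve as the baseline record of pain and anxiety.* Then state that the day-1 and day-30 totals will be compared by ANCOVA with the baseline total as covariate, with a missing-baseline indicator for patients enrolled before the change. No new endpoint is needed.

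The cost is a few extra minutes per patient at an assessment where part of the form is already used. About 60 patients recruited by October 2018 would have no baseline total, which leaves at most 540 of 600 who could provide one. That number falls with every patient operated on before the change.

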#### Intraoperative data

Intraoperative physiological data will be extracted from the operating room monitors using a custom-designed computer programme. Collected data will include heart rate, blood pressure, oxygen saturation, temperature, end-tidal carbon dioxide and volatile anaesthetic concentrations and the frontal EEG waveform and quantitative EEG indices. Additional EEG information will be obtained for a subgroup of consenting participants to investigate multichannel EEG features.

Effect-site concentrations of fentanyl and desflurane will be calculated and further EEG processing performed in real time. The oscillatory EEG alpha magnitude and dose-response relationships will be displayed to verify the oscillatory EEG alpha optimisation intervention.

The anaesthetic record will be photocopied so as to have a record of all administered medications. Pertinent event data, such as regional anaesthesia, estimated blood loss, total intravenous fluid volume administered and urinary catheterisation will be recorded routinely.

### Data management

Baseline data and clinical outcome data will be entered and managed using REDCap electronic data capture tools hosted at the University of Auckland, New Zealand. REDCap (Research Electronic Data Capture) is a secure, web-based application designed to support data capture for research studies, providing (1) an intuitive interface for validated data entry; (2) audit trails for tracking data manipulation and export procedures; (3) automated export procedures for seamless data downloads to common statistical packages and (4) procedures for importing data from external sources [29]. Intraoperative vital sign and EEG time-series data will be saved in real time to a computer used solely for data collection. At the end of a participant’s anaesthesia, the files will be transferred and stored on a secure server.

### Data safety monitoring

Risks to participants are expected to be minimal; the interventions being trialled are within the realms of current anaesthetic practice and the case anaesthetist will have the autonomy to digress from protocol in clinical interests of patients, e.g. if the doses suggested seem outside acceptable clinical practice. The primary risks that have been identified are light anaesthesia (with increased but still very low risk of awareness with recall) or deep anaesthesia and inadequate or excessive intraoperative analgesia. These risks will be measured and mitigated by the use of agreed dosage upper and lower limits, quantitative EEG monitoring, and interim analysis of PACU pain data. No formal interim analyses are planned; however, we will be taking informal feedback from clinicians throughout the trial and will review any unanticipated issues which arise.

A data safety monitoring committee will consist of two independent anaesthetists with research expertise. Any adverse events will be recorded and then categorised as to severity and the likelihood of the event having occurred as a result of the study. Adverse events will be reviewed regularly by the committee and the committee will make recommendations to the research team. Should any serious adverse events occur which are deemed due to the study itself, these will be communicated immediately to the committee to consider whether the trial should be suspended.

### Statistical analysis and power calculations

We intend to recruit 600 participants. The 2 × 2 factorial design will result in 300 patients assigned to the maintenance phase intervention and 300 to the emergence phase intervention (see Fig. 1). This will ensure that the study will be well-powered for the primary EEG outcomes and sufficiently powered to detect moderate-large effects in the secondary clinical outcomes. Our primary analyses will be intention to treat; however, per-protocol analyses will also be reported. For the primary outcome for the maintenance phase *Alpha Max* intervention, alpha power in groups A and B (Fig. 1) pooled together will be compared to groups C and D. For the primary outcome for the emergence phase intervention, groups A and C (Fig. 1) will be compared to groups B and D pooled. The crude difference will be reported as the primary outcome; however, an adjusted estimate will also be provided for the emergence outcome. This will include an interaction term for the maintenance phase intervention, since one might reasonably expect alpha power in the emergence phase to correlate with alpha power in the maintenance phase.

EEG analysis will be performed using customised script in MATLAB. Our previous summary data suggest that a mean oscillatory alpha power of 4.75 dB with standard deviation of 2.1 dB might be expected in a general surgical population. Therefore, an estimated 230 patients are required to have 95% power to detect an increase in oscillatory alpha of at least 1 dB (equivalent to ~ 20% relative increase in alpha power in response to the fentanyl) in the intervention group compared with the control group (two-tailed alpha 0.05, beta 0.05); thus, with a planned total of 300 patients per group we are comfortably overpowered for this outcome.

PACU delirium is our clinical outcome of primary interest, as a marker of neurocognitive recovery from anaesthesia. In our previous observational study, the incidence of CAM-ICU-diagnosed PACU delirium was 16% in those over 60 years and in a subsequent departmental audit, the incidence of PACU delirium diagnosed using the NuDESC tool was around 20% in those aged 65 years and over. Given that the study inclusion criteria requires > 2 h of anaesthesia, study participants will likely in general be having more extensive surgery and longer anaesthesia than those in the previous study and audit; therefore, we conservatively estimate a 20% incidence of PACU delirium in the control groups. From our observational work, the presence of EEG alpha has an odds ratio of approximately 0.5 for PACU delirium (unpublished data). Five hundred and thirty-two patients would be required to demonstrate a decrease in PACU delirium from 20 to 10% with 90% power (two-tailed alpha 0.05, beta 0.1, *χ*^2^ test). Thus, the study is powered to demonstrate strategies which have a large impact in preventing the development of delirium.

Almost certainly this study will also be sufficiently powered for minimum clinically important effects in some of the other secondary outcomes including delirium subcomponent features, days alive and out of hospital, and quality of recovery. We plan to recruit 600 patients to allow for loss to follow-up and a lower incidence of delirium than expected.

Continuous outcomes will be assessed using *t* tests and analysis of variance (ANOVA), ordinal with rank sum, and categorical outcomes will be assessed using the *χ*^2^ test, with significance set at *p* < 0.05. Non-linear mixed-effect modelling will be incorporated where appropriate to account for propensities such as: patient maximum alpha power, within-patient fentanyl and desflurane dose-response relationships and characteristics of the anaesthetic technique. Interactions between the two interventions are possible and will be examined. We also plan to carry out multivariate logistic regression to determine the major risk factors for the development of the features of PACU delirium, and receiver operator curve analysis to determine which elements of the early delirium screening tools are most closely associated with adverse clinical outcomes. *We anticipate performing further exploratory analyses in addition to those explicitly defined pre-operatively.*

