We have previously found that delirium (or incomplete neurocognitive recovery) in the recovery room seems to occur less often when patients display stronger alpha (7–17 Hz) oscillations in the frontal EEG during the emergence phase of anaesthesia [5, 6]. However, frontal EEG alpha power during maintenance of anaesthesia is negatively correlated with pre-operative cognitive impairment [7] and with advancing age [8–10], and this could explain the propensity for postoperative delirium. Nevertheless, the extent to which the EEG alpha oscillation is subject to intraoperative pharmacological manipulation has, thus far, gone largely unexplored.

Previous EEG-based protective strategies have focussed on targeting proprietary dimensionless index values, the meaning of which are not well understood. However, the EEG alpha oscillation is a specific hallmark of gamma-amino-butyric-acid (GABA)-ergic anaesthesia [11]. Marked loss of frontal EEG alpha activity can occur in response to noxious stimulation [12, 13] and the frequency and power of alpha oscillations are sensitive to changes in effect-site concentrations of volatile agents and opioids [8, 14]. We hypothesise that a maximal EEG alpha oscillation during general anaesthesia may represent an ideal anaesthetic state of both adequate anti-nociception and appropriate anaesthetic depth, which would represent a novel, individualised, anaesthetic strategy.

We also plan to investigate the efficacy of an alternative strategy; transition to propofol during the emergence phase of anaesthesia on the EEG patterns observed during emergence from anaesthesia, with the aim of preventing abrupt transitions in brain state. This intervention has been shown to reduce the incidence of emergence delirium in young children [15, 16] but has not been investigated adequately in older populations. As well as looking at EEG features and trajectories, we will evaluate the effect of these interventions on relevant clinical outcomes, particularly the incidence of delirium in the post-anaesthesia care unit (PACU).

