### Randomisation and blinding

Assignment of study participants to intervention groups will be performed using block randomisation [17], stratified by cognitive status (determined by pre-operative Montreal Cognitive Assessment (MOCA) score), surgery type (vascular, orthopaedic and general/other) and site. Pre-operative cognitive impairment is widely recognised as a risk factor for postoperative delirium and we have previously found that delirium risk appears to be lower for non-spinal orthopaedic procedures [6]. The researcher collecting intraoperative EEG data will perform the randomisation, shortly prior to commencement of the anaesthesia episode. The case anaesthetists will not be blinded to the interventions. Participants will be blinded to their interventions. Members of the research team responsible for recruitment, baseline data collection and clinical outcome data observers for the PACU scores and follow-up data collection will be blinded to randomisation groups and intraoperative events. For final analysis of the primary EEG outcomes, the raw EEGs will be de-identified so that the researcher conducting the analysis cannot identify the individual participant or the group allocation. We do not anticipate unblinding will be necessary.

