### First randomisation: maintenance phase of anaesthesia

Participants will be randomised to intraoperative oscillatory EEG alpha optimisation (Intervention 1) versus standard care (with burst suppression alert).

Intervention 1 involves real-time acquisition of oscillatory alpha power from the frontal EEG (recorded with the standard EEG electrode strip from the Entropy Module (GE Healthcare, Chicago, IL, USA) or the Bispectral Index (BIS) (Medtronic, Minneapolis, MN, USA) or other quantitative EEG monitor. An individual patient value for the maximal oscillatory alpha power ‘*Alpha Max*’ will be determined following induction of anaesthesia by variation of the end-tidal desflurane concentration prior to surgical incision. Effect-site concentrations of volatile and opioid will be estimated in real time to inform decisions around drug titration. During the intraoperative phase, we will aim to maximise oscillatory alpha EEG activity by individualised titration of desflurane and opioid. If alpha activity suddenly drops, the case anaesthetist will be advised to give a 0.5–1 mcg/kg bolus of fentanyl. Target end-tidal desflurane concentration will be adjusted according to real-time dose-response information. Typically, the concentration will be reduced in response to sustained loss of alpha activity; however, desflurane will not be reduced if quantitative EEG indices exceed a pre-defined threshold, to avoid awareness. For example, the State Entropy (SE) from the GE Entropy Module will be maintained below 60. The *Alpha Max* target will be adjusted intraoperatively if a new maximum is reached at any stage. The titrations will occur within prearranged limits agreed by the research team and the case anaesthetist and taking into account the clinical context, for example the degree of surgical stimulation.

For those patients randomised to standard care, anaesthesia will be conducted as per usual care by the anaesthetist, with quantitative processed EEG index values (e.g. State Entropy) and EEG waveforms visible as per the standardised protocol).

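### The primary EEG comparisons are fixed as crude differences although randomisation is stratified on prognostic factors, so they are conservative and less precise than they need be

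*Protocol article*

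**What the plan says.** Under Randomisation and blinding, allocation is by blocks, "stratified by cognitive status (determined by pre-operative Montreal Cognitive Assessment (MOCA) score), surgery type (vascular, orthopaedic and general/other) and site". That section justifies the choice by delirium risk: cognitive impairment raises it, and non-spinal orthopaedic surgery appears to carry less of it. For alpha power, Background and rationale states that "frontal EEG alpha power during maintenance of anaesthesia is negatively correlated with pre-operative cognitive impairment [7] and with advancing age".

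The section on statistical analysis and power calculations then pools the factorial margins (A and B against C and D for maintenance, A and C against B and D for emergence) and fixes the estimator: "The crude difference will be reported as the primary outcome; however, an adjusted estimate will also be provided for the emergence outcome". Of the adjusted emergence estimate it says only: "This will include an interaction term for the maintenance phase intervention". No stratification factor or baseline covariate is named. For tests, it lists for continuous outcomes *t* "tests and analysis of variance (ANOVA), ordinal with rank sum, and categorical outcomes will be assessed using the" χ² test.

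Three other provisions come near the point. The NSQIP risk score is collected for possible risk adjustment. Mixed-effect modelling is to be used where suitable, with patient maximum alpha, dose-response and technique as the named terms. A multivariable logistic regression is planned to find risk factors for delirium features. None is tied to the primary treatment comparison or to the strata.

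**The concern.** Stratified blocks force balance between arms on the stratification factors, so differences between strata add almost nothing to the true sampling error of the treatment difference. A two-sample *t* test does not know this. It leaves the between-stratum variance in its error term and reports a standard error larger than the true one. The interval then covers more than 95%, and the test rejects less than 5% of the time under the null.

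A baseline predictor that was not stratified on, such as age, is a different case. The crude interval then has correct coverage, and adjustment simply gives a shorter valid one.

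This is not a detail left to an analysis plan that is not shown. The article names the crude difference as the primary result, so an analysis plan that made an adjusted estimate primary would depart from it. The trial describes itself as largely exploratory, with the modifiability of the EEG unknown. A precise estimate of effects that may be smaller than 1 dB is therefore much of what it can deliver.

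**Working it through.** **Inputs from the protocol article:** SD 2.1 dB, target difference 1 dB, two-sided 5% level, 95% power, 230 patients required; 300 against 300 on each factorial margin; PACU delirium 20% against 10%, 90% power, 532 required, 600 planned.

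**Assumed:** R², the share of alpha-power variance explained by the strata or baseline covariates. The documents give none, so a range is shown.

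**1. The plan's own figures.** For alpha power, n per arm = 2 × (1.960 + 1.645)² × 2.1² / 1² = 114.6, so 115 per arm and 230 in total, as stated. For delirium, the two-proportion formula with pooled variance and no continuity correction gives 266 per arm and 532 in total, as stated. Both sample sizes come from unadjusted formulas.

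**2. Crude precision at 300 against 300.** SE = 2.1 × √(2/300) = 0.1715 dB; 95% half-width = 1.96 × 0.1715 = 0.336 dB. Power at 1 dB = Φ(1/0.1715 − 1.96) = 99.99%. Power at 0.5 dB = Φ(0.5/0.1715 − 1.96) = 83%.

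**3. Effect of adjustment.** Adjusted SE = 0.1715 × √(1 − R²). Excess width of the crude interval = 1/√(1 − R²) − 1. Actual level of the crude test, if all of R² lies in the balanced strata = 2 × [1 − Φ(1.96/√(1 − R²))]. Number of patients a crude analysis would need to match = 600/(1 − R²).

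| Assumed R² | Adjusted half-width (dB) | Crude interval wider by | Actual crude level (strata only) | Crude N to match | Adjusted power at 0.5 dB |
|---|---|---|---|---|---|
| 5% | 0.328 | 2.6% | 4.4% | 632 | 85% |
| 10% | 0.319 | 5.4% | 3.9% | 667 | 87% |
| 20% | 0.301 | 11.8% | 2.8% | 750 | 90% |
| 30% | 0.281 | 19.5% | 1.9% | 857 | 94% |

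**4. A refinement on power.** The 83% treats the crude SE as the true sampling SD. Where the variance lies in balanced strata, the estimate is less variable than that, and crude power is Φ((0.5 − 0.336)/adjusted SE). This is Φ(0.164/0.1627) = 84% at R² of 10% and Φ(0.164/0.1534) = 86% at 20%. The gain from stratum terms alone is therefore 84% to 87%, or 86% to 90%. For an unstratified covariate it is 83% to 87%, or 83% to 90%.

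**5. Simulation check.** 600 patients were allocated in permuted blocks of 4 within 18 assumed strata (2 cognition × 3 surgery × 3 sites), with 3,000 runs per setting.
- With strata explaining 10% of variance, the crude test reported an SE of about 0.171 against a true sampling SD of about 0.163, and rejected 3.5% to 4.0% of the time under the null.
- With 20%, the true SD was about 0.152 and rejection was 2.6% to 2.8%.
- The model with strata and one covariate rejected 4.3% to 5.7%.
- With strata at 20% and a further covariate at 10%, power at 0.5 dB was 86% crude and 94% adjusted.

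**6. PACU delirium.** Power of the χ² test at 300 against 300 is 93.1% for 20% against 10%. A simulation (1,500 runs) used one baseline covariate with an assumed SD of 0.5 or 1.0 on the log-odds scale, without stratified allocation. χ² against adjusted logistic power was 93% against 94% and 93% against 96% at 20% v 10%. At 20% v 12.5% it was 71% against 74% and 70% against 75%.

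**The case against.** The best reply is that the error runs in the safe direction. The crude estimate is unbiased, false positives are not inflated, and at 1 dB the trial has power to spare with or without adjustment. All of that stands, and it limits how serious the point is. It does not make the reported intervals correct.

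A second reply is that covariate lists belong in the analysis plan and that the wording on the adjusted emergence estimate need not be exhaustive. That is fair for the supplementary estimate, and a reader should not infer that the loose provisions for mixed models and NSQIP rule out any adjusted maintenance analysis. None of them displaces the crude difference as the primary result.

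Several stronger readings are tempting but not supported:

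- **That primary comparisons rest on a χ² test.** Both primary outcomes are continuous alpha power. The χ² test covers categorical outcomes, and PACU delirium is listed as secondary.
- **That delirium has no power to spare.** The plan needs 532 and recruits 600, with about 93% power at the planned rates before losses. Nor does the argument about interval width carry over to a conditional odds ratio, where adjustment raises power without narrowing the interval.
- **That the crude interval is miscalibrated for every predictor.** This applies only to variance in the balanced strata. Cognitive status is the only stratification factor that the article links to alpha power; the evidence on surgery type concerns delirium. The 30% row, read as a property of the strata alone, has no support in the text.
- **That monitors shift alpha power by site.** The article allows Entropy, BIS "or other quantitative EEG monitor", but does not say that devices differ between sites or give different alpha power.

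**Conclusion.** The point holds as one of efficiency and calibration for the two primary EEG analyses. The article fixes a crude primary estimator after stratifying on factors of which at least one, by its own account, predicts alpha power. If the strata explain 10% or 20% of the variance, the crude interval is about 5% or 12% too wide and the true two-sided error about 3.9% or 2.8%. If they explain little, little is lost. Age adds precision only.

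A reader might infer that the primary results would be invalid or the trial underpowered. Neither follows: the estimate is unbiased and power at 1 dB is above 99.9% either way. What can be gained is a shorter, correctly calibrated interval and better sensitivity below 1 dB. For PACU delirium the gain is a few percentage points of power. The plan should be changed, but this is not a flaw on which the trial stands or falls.

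**What to change.** For each primary EEG outcome, make the primary analysis a linear model of oscillatory alpha power with both randomised factors as main effects, MOCA stratum, surgery type and site, and age as a prespecified baseline covariate. Include no variable measured after randomisation: not *Alpha Max*, not achieved drug concentrations and, for emergence, not maintenance alpha power. Report the crude difference as supportive, and the interaction between interventions separately.

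As a secondary extension, replace the unstratified χ² test for PACU delirium by logistic regression with the same terms or a Cochran-Mantel-Haenszel test by stratum.

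The cost is a change of wording, to be made before any unblinded analysis. The stratification factors and standard demographic data are already collected. Some strata may be small: under the 18 strata assumed above, 600/18 is about 33 patients each and, at 15% delirium (midway between 20% and 10%), about 5 events. A rule for pooling should therefore be set in advance. Entering the factors as main effects rather than as crossed strata eases this in the regression models.
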